## Assessment of Severity

Severity should be recorded and graded according to the Division of AIDS Table for Grading the Severity of Adult and Pediatric Adverse Events (DAIDS) Version 2.0 November 2014.

## Investigator Requirements for Reporting Adverse Events and Serious Adverse Events

### Reporting to UCSF Committee on Human Research (CHR / IRB)

All SAEs and unexpected AEs of relation greater than unrelated must be reported within 5-working-days of PI awareness using the Adverse Event Reporting Form on the UCSF CHR website (iRIS).

### Reporting to UCLA

Reporting to UCLA Data Safety Monitoring Board (DSMB)

All SAEs and unexpected AEs meeting reportable criteria in the Data Safety Monitoring Plan (DSMP) must be reported within 10-working-days of PI awareness. A summary letter must include detailed accounts of the following:

- Summary of SAE
- Resolution
- Study Drug
- Attribution
- Notification

### Reporting to NIH – National Institute of Drug Abuse (NIDA) through the Serious Events Tracking and Reporting System (SAETRS)

All SAEs meeting reportable criteria in the DSMP must be reported within 10-working-days of PI awareness. If SAE is fatal, it must be reported within 2-working-days of PI awareness.

### Investigator Requirements and Instructions for Reporting Adverse Events and Serious Adverse Events to Gilead

*Adverse Events*

The investigator shall report SAEs that occur during treatment and within 30 days of last dose of study drug to Gilead quarterly in the format of a Study Progress Report.

*Serious Adverse Events*

All SAEs, regardless of cause or relationship, that occur from enrollment until 30 days after the last dose of study drug shall be reported to Gilead Sciences DSPH within 10 working days of PI awareness. If SAE is fatal, it shall be reported within 2 working days of PI awareness. If the investigator learns of any SAEs that occur after study participation has concluded and the event is deemed relevant to the use of study drug, he will promptly document and report the event to Gilead Sciences DSPH.

## Special Situations Reports

### Definitions of Special Situations

Special situation reports include all reports of medication error, abuse, misuse, overdose, lack of effect reports and pregnancy reports regardless of an associated AE.

Medication error is any unintentional error in the prescribing, dispensing, or administration of a medicinal product while in the control of the health care provider, subject, or consumer.

Abuse is defined as persistent or sporadic intentional excessive use of a medicinal product by a subject.

Misuse is defined as any intentional and inappropriate use of a medicinal product that is not in accordance with the protocol instructions or the local prescribing information.

An overdose is defined as an accidental or intentional administration of a quantity of a medicinal product given per administration or cumulatively which is above the maximum recommended dose as per protocol or in the product labelling (as it applies to the daily dose of the subject in question). In cases of a discrepancy in drug accountability, overdose will be established only when it is clear that the subject has taken the excess dose(s). Overdose cannot be established when the subject cannot account for the discrepancy except in cases in which the investigator has reason to suspect that the subject has taken the additional dose(s).

Product complaint is defined as complaints arising from potential deviations in the manufacture, packaging, or distribution of the medicinal product.

### Instructions for Reporting Special Situations

#### **Instructions for Reporting Pregnancies**

The investigator should report pregnancies in female study subjects that are identified after initiation of study drug and throughout the study, including the post study drug follow-up‑ period, to Gilead Sciences DSPH using the pregnancy report form within 10 working days of becoming aware of the pregnancy.

The pregnancy itself is not considered an AE nor is an induced elective abortion to terminate a pregnancy without medical reasons.

Any premature termination of pregnancy (eg, a spontaneous abortion, an induced therapeutic abortion due to complications or other medical reasons) will be reported within 10 working days as an SAE. The underlying medical reason for this procedure should be recorded as the AE term.

A spontaneous abortion is always considered to be an SAE and will be reported as described in Sections 8.4.4. Furthermore, any SAE occurring as an adverse pregnancy outcome post study will be reported to Gilead Sciences DSPH.

The outcome of the pregnancy should be reported to Gilead Sciences DSPH using the pregnancy outcome report form.

#### **Reporting Other Special Situations**

All other special situations will be reported as AEs or SAEs and reported accordingly. These reports must consist of situations that involve study drug but do not apply to non-Gilead concomitant medications.

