# ADVERSE EVENTS MANAGEMENT

## Definition of Adverse Events, Adverse Reactions, and Serious Adverse Events

### Adverse Event

An adverse event (AE) is any untoward medical occurrence in a clinical study subject administered a pharmaceutical medicinal product, which does not necessarily have a causal relationship with the treatment. An AE can therefore be any unfavorable and/or unintended sign, symptom, or disease temporally associated with the use of a medicinal product, whether or not considered related to the medicinal product. AEs may also include pre- or post‑treatment complications that occur as a result of protocol specified procedures, lack of efficacy, overdose, substance use, or occupational exposure. Preexisting events that increase in severity or change in nature during or as a consequence of participation in the clinical study will also be considered AEs.

An expected adverse event is an AE that may be reasonably anticipated to occur as a result of the study procedures or study participation or is part of the normal disease process or progression.

An unexpected adverse event is defined as being unexpected if the event exceeds the nature, severity, or frequency described in the current Committee on Human Research (CHR) application including the protocol, consent form and investigator brochure, when applicable. An unexpected AE also includes any AE that meets the following criteria:

- Results in subject withdrawal from study participation
- Due to an overdose of study medication
- Due to a deviation from CHR-approved study protocol

An AE does not include the following:

- Medical or surgical procedures (e.g., surgery, endoscopy, tooth extraction, transfusion) performed; the condition that leads to the procedure may be an adverse event and must be reported.
- Pre-existing diseases or conditions or laboratory abnormalities present or detected during or before screening that do not worsen
- Situations where an untoward medical occurrence has not occurred (e.g., hospitalization for elective surgery, social and/or convenience admissions)
- Overdose without clinical sequelae (see Section 8.5)
- Any medical condition or clinically significant laboratory abnormality with an onset date before enrollment and not related to a protocol-associated procedure is not an AE. It is considered to be pre-existing and should be documented on the medical history.
- Substance use or admission to substance use treatment
- Incarceration

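### A harmless study-drug overdose, misuse, abuse or medication error is excluded from AEs in Section 8.1.1 but must be reported as an AE or SAE under Section 8.5.2

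*Protocol*

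**What the plan says.** Section 8.1.1 (Adverse Event) rests on a medical occurrence: "An adverse event (AE) is any untoward medical occurrence in a clinical study subject administered a pharmaceutical medicinal product". It then gives a list introduced by "An AE does not include the following". Two entries matter here: "Overdose without clinical sequelae (see Section 8.5" and "Situations where an untoward medical occurrence has not occurred". The same section names criteria that make an AE unexpected, one of which is "Due to an overdose of study medication".

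Section 8.5.1 (Definitions of Special Situations) sets the scope: "Special situation reports include all reports of medication error, abuse, misuse, overdose, lack of effect reports and pregnancy reports regardless of an associated AE". It defines misuse as follows: "Misuse is defined as any intentional and inappropriate use of a medicinal product that is not in accordance with the protocol instructions" or with local prescribing information.

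Section 8.5.2 gives pregnancy its own form and deadline and says that pregnancy itself is not an AE. For the rest, under Reporting Other Special Situations, it states: "All other special situations will be reported as AEs or SAEs and reported accordingly". The only limit added there is that study drug must be involved.

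**The concern.** Section 8.1.1 sends the reader to Section 8.5 for overdose without consequences, and Section 8.5 reverses what Section 8.1.1 has just said. A staff member who follows the cross-reference cannot comply with both.

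Two things are at stake. The first is the AE record: the same event may be entered as an AE on one occasion and left out on another, depending on which section was consulted. The second is onward reporting. Once a study-drug overdose counts as an AE, it meets a criterion for an unexpected AE in Section 8.1.1. The section on reporting to the UCSF committee requires unexpected AEs judged more than unrelated to be reported within 5 working days. If the event was never an AE, that duty does not arise by this path.

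**Working it through.** No arithmetic applies. The question is whether the rules can be followed together, so they are set side by side for each kind of event.

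| Event | Section 8.1.1 | Sections 8.5.1 and 8.5.2 | Agree? |
|---|---|---|---|
| Study-drug overdose with clinical consequences | The consequence is an AE | Special situation, reported as AE or SAE | Yes |
| Study-drug overdose without clinical consequences | Expressly not an AE | Special situation, reported as AE or SAE | No |
| Misuse, abuse or medication error with study drug, no untoward occurrence | Not an AE: outside the definition and on the exclusion list | Special situation, reported as AE or SAE | No |
| Pregnancy itself | Not on the exclusion list | Own form and deadline; expressly not an AE | No conflict |
| Overdose of a non-Gilead concomitant drug, no consequences | Not an AE under the general exclusion | Outside the reporting rule | Yes |

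1. **Overdose.** The conflict in the second row is direct. The exclusion in 8.1.1 names the event and points to 8.5. Section 8.5.1 brings it in regardless of any associated AE, and 8.5.2 makes no exception for absence of harm.

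2. **Misuse, abuse and medication error.** The conflict in the third row comes from the general exclusion of situations without an untoward medical occurrence. It is real for misuse because the protocol gives instructions that can be breached deliberately without harm. The section on dosage and administration tells subjects to keep roughly the same interval between doses and not to double up after a missed one. Intentional and inappropriate use against such an instruction is misuse under 8.5.1, and an AE under 8.5.2, with no medical event.

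3. **Consequence for the IRB.** Under 8.5.2 a harmless overdose is an AE. It is due to an overdose of study medication, so 8.1.1 makes it an unexpected AE. The 5-working-day rule then applies if the relation is judged greater than unrelated. Under the exclusion in 8.1.1 the chain stops at the first step.

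4. **Size.** Each event in the second or third row is 0 AE records under 8.1.1 and 1 under 8.5.2. The protocol gives no rate of overdose, misuse, abuse or medication error, so no total can be derived.

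5. **Endpoints.** The acceptability analysis (Primary Analysis) takes adherence from observed doses and WisePill data. It does not use AE records, so it is the same under either reading.

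**The case against.** The best defence is that 8.5.2 only borrows the AE reporting route and does not reclassify the event. That is possible, but the text does not say so. It orders these events to be reported as AEs or SAEs and separately to be reported accordingly; the second part already covers the route. No other form or category is provided for them. The defence does show that a clarification may suffice, without any change of policy.

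A reader might also infer more than the documents support:

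- **A distorted safety comparison between arms.** AEs are not among the primary, secondary or other endpoints, and the data analysis section plans no between-arm AE analysis. Unequal detection is not established either: the unobserved arm has WisePill transmission and weekly pill counts.
- **Adherence failures in general becoming AEs.** Misuse must be both intentional and inappropriate. A missed dose is not plainly a use of the drug, and the catch-up dosing that the protocol allows in the mDOT arm follows its instructions.
- **Virologic failure becoming a reportable drug-related AE.** Nothing equates virologic failure with a lack-of-effect report, and Section 8.2.1 says ineffective treatment should not be considered causally related in AE reporting.
- **Escalation to the DSMB.** That depends on criteria in the Data Safety Monitoring Plan, which is not at hand.
- **A count of spurious AEs.** Any figure would rest on invented rates.

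**Conclusion.** The contradiction stands, and no passage of the protocol resolves it. For a study-drug overdose, medication error, abuse or misuse without harm, Section 8.1.1 and Section 8.5.2 give opposite instructions. What is entered as an AE, and whether a harmless overdose judged more than unrelated is treated as an unexpected AE for the IRB, depends on the section consulted.

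This is a minor point. It affects the consistency of safety recording and reporting, not the adherence endpoints or the primary conclusions. Its numerical effect cannot be estimated from the document. The conclusion assumes that 8.5.2 means what it literally says; if only the route was intended, the fault is one of wording, but the text still needs correcting.

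**What to change.** Reconcile Sections 8.1.1, 8.5.1 and 8.5.2 in one direction:

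- **Option A.** State in 8.5.2 that medication error, abuse, misuse, overdose and lack-of-effect reports are reported as special situations, and that an AE or SAE is recorded only when an untoward medical occurrence is associated. This option must also name a form, a recipient and a deadline. At present the AE/SAE path is the only route 8.5.2 gives these events, so removing it without a replacement would leave them with none.
- **Option B.** If the sponsor does want these events recorded as AEs without harm, remove the overdose exclusion from 8.1.1 and qualify the general exclusion so that it does not cover special situations.

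Under either option, list special situations separately from AEs, so that a reader can tell a medical event from a drug-handling event.

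The cost is a few sentences, one listing and, for Option A, one added reporting route and slightly fewer records counted as AEs. No event is lost under Option A, provided the new route is written in.

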# STATISTICAL CONSIDERATIONS

## Analysis Objectives and Endpoints

### Analysis Objectives

The primary objectives of this study are:

- To assess the feasibility of treating active PWIDs for HCV with LDV/SOF by mDOT versus weekly dispensing, with MI adherence counseling, as measured by recruitment and retention rates, overall and by arm.
- To evaluate the acceptability of mDOT versus weekly dispensing, with MI adherence support, among PWIDs treated with LDV/SOF, as determined by mDOT and MI participation rates, medication adherence rates and the proportion of subjects that complete therapy, by arm.
- To assess through in-depth, semi-structured qualitative interviews, the challenges with time intensity required for mDOT and weekly dispensing interventions, and identify key factors affecting treatment adherence for PWIDs treated with LDV/SOF.

The exploratory objectives of this study are:

- To assess end-of-treatment response and SVR, as determined by the proportion with undetectable HCV RNA at weeks 8 and post treatment week 12, by arm.
- To assess adherence to treatment by weekly SOF metabolite levels, by arm, If SVR, retention and/or medication adherence data suggestion medication compliance issues.
- To assess drug use behaviors before and after HCV treatment.
- To assess HCV relapse and reinfection at post treatment week 36 among participants achieving SVR.
- To evaluate demographic, behavioral and HCV strain correlates of adherence and SVR.
- To characterize the social and PWID networks of participants in preparation for a subsequent full TasP trial.

### Primary Endpoints

- Screen to eligibility ratio, overall
- Eligibility to enrollment rate, overall
- Retention rates, overall and by arm
- Study completion rates, overall and by arm
- Medication adherence rates and the proportion of subjects that complete therapy, overall and by arm
- Barriers and facilitators to HCV treatment

### Secondary Endpoints

Secondary endpoints include the following:

- SVR, as determined by the proportion with undetectable HCV RNA at weeks 8 and post treatment week 12, by arm
- SOF metabolite levels, by arm, as needed based on results.
- HCV risk behaviors and substance use before and after HCV treatment
- HCV relapse and reinfection at post treatment week 36 among participants achieving SVR.

### Other Endpoints of Interest

Additional evaluations will explore demographic, behavioral and HCV strain correlates of adherence and SVR; and analyses exploring at the social and PWID networks of participants in preparation for a subsequent full TasP trial.

## Analysis Conventions

All individual subject data will be listed as measured. All statistical summaries and analyses will be performed using STATA^®^ software. The study drug in this study is LDV/SOF. Last dose of study drug refers to the last dose of LDV/SOF and will be used in the definition of treatment-emergent AEs and laboratory abnormalities as well as the efficacy endpoints of SVR at various post-treatment time points. Between group analyses will be conducted using intention-to-treat analyses without regard to study procedure compliance.

## Demographic Data and Baseline Characteristics

Demographic and baseline characteristics will be summarized using standard descriptive methods by treatment group and overall.

Demographic data will include sex, self-identified race/ethnicity, and age.

Baseline characteristic data will include body mass index, HCV RNA level (log_10_ IU/mL) and additional endpoints as necessary.

## Data Analysis

### Primary Analysis

### Feasibility: Feasibility of treating active PWIDs for HCV with LDV/SOF by mDOT versus unobserved dosing will be measured by recruitment and retention rates overall and by arm. We will calculate the following feasibility measures: 1) proportion of those eligible among those screened; 2) proportion enrolled among those eligible; and 3) study retention and completion rates, overall and by arm. Process measures (e.g., visit length) and reactions to study procedures will also be assessed. Descriptive statistics will be presented with 95% confidence intervals, to help in interpretation. Between-group differences in retention and completion will be assessed using Fisher’s exact and Wilcoxon tests. We will also calculate Kaplan-Meier curves for time to dropout, by group, and test for differences using the log-rank test.

**Acceptability:** The acceptability of mDOT versus unobserved dosing, the percent of treatment medication adherence to LDV/SOF, will be measured by the percent of doses taken overall (observed and unobserved), will be assessed using DOT doses and weekend WisePill data for the mDOT arm, and WisePill data for the unobserved dosing arm. Other outcomes of interest will include completion of therapy, patterns of adherence, and time to stopping medication. Concordance of the various adherence measures will be examined using weighted Kappa and intraclass correlations. Between-arm differences will be assessed using Fisher’s exact and Wilcoxon tests for outcomes measured once, and GEE models for repeated outcomes. We will also use GEE models to compare WisePill openings and pill counts, accounting for between-arm differences in expected frequency.

Inter-rater reliability: To ensure reliability and validity in open-ended component of the in-depth interviews analysis, we will implement a verification strategy to ensure self-correction throughout the analysis process. The two coders will assess inter-rater reliability by calculating the correlation between a set of ratings done by two independent raters for the initial set of 3-6 transcripts, and then again on the next set of 6 transcripts. After each inter-rater reliability assessment, the codebook and codes will be revised based on reconciliation of findings done between coders. Inter-rater reliability will be assessed as a team twice during the analysis process and again at the end of analysis as a post-hoc evaluation of reliability and validity. This evolving analysis process will ensure high quality of research decisions, the rationale behind decisions, and the responsiveness of investigators to the data. Once the codebook is developed and verified all remaining transcripts will be coded. Further meetings will be held to discuss any differences in coding and to ensure consistency in the application of codes.

Final analysis will begin with data reduction, then display, analysis and conclusion drawing using a conceptual framework in which hypothesized factors affecting adherence are assessed and unanticipated findings are identified. The analytic team will work from the coded data to merge findings into a final summary and a consensus of major themes, relationships between themes, and ranking of items of most importance to adherence. This method of data reduction encompassing both site and team based analysis creates a robust iterative process through which the data is thoroughly discussed and analytical consensus achieved. Atlas.ti software will be used to both code and develop data displays used in the analysis for this study.

### Exploratory Analyses

While we recognize the small sample size limits our ability to draw firm conclusions from exploratory analyses, the paucity of data for this treatment approach allows for hypothesis-generating results.

End-of-treatment response and SVR: We will compare the proportion of participants with undetectable HCV RNA at weeks 8 and post-treatment week 12 between arms using Fisher’s exact tests.

Acceptability based on drug levels: Depending on resource availability and SVR rates, we may calculate rates of LDV and/or SOF metabolite-positivity by week in both arms; between-group differences will be compared using GEE models for repeated outcomes.

HCV relapse and reinfection: Among participants who achieve SVR, we will determine the proportion who experience HCV relapse and reinfection at post-treatment week 36, overall and by arm, with exact 95% confidence intervals.

Social and PWIDs network analyses to inform a subsequent full TasP trial: We will characterize injector network sizes at baseline and follow-up. Newman’s method will be used to calculate assortativity coefficients, a measure of the degree of demographic and risk behavior similarity within networks. These findings will help us determine whether a full efficacy trial should use targeted sampling strategies to ensure diversity in network sizes, and whether randomization should be stratified by one or both of these factors in future trials.

Other Exploratory Outcomes:

Drug use behaviors before and after HCV treatment: Recent data suggest significant changes in drug use behaviors after HCV diagnosis: serosorting with other HCV-positive PWIDs and a sustained reduction in drug use. We will assess these behaviors at baseline and follow-up for preliminary estimates of the possible impact of HCV treatment on these behaviors. ANCOVA and conditional logistic models will be used for continuous and binary outcomes respectively.

Correlates of Adherence and SVR: We will explore demographic, behavioral correlates of medication adherence using GEE models for repeated measures. In addition, we will explore demographic and behavioral correlates of SVR using Fisher exact tests and exact logistic regression.

